## Discussion

This trial is one of the first in its kind, to compare different sorts of mesh types in a randomized controlled setting. Lots of mesh devices are available for herniorraphy made by various companies. Often the choice of the mesh depends on the personal favour of the operating surgeon. The reason to start with this trial is to have a more scientific approach for the decision-making regarding the determination of mesh device.

In this study protocol only the patient is blinded for the treatment. By all means, the operating surgeon cannot be blinded for the type of mesh. The doctor who sees the patients in the outpatient clinic, and fills in forms D2 an D3 can be blind for the treatment type. Because of logistical reasons this is not added to this study protocol. Besides the logistical reasons we think that there is little value in blinding the treating doctor in the outpatient clinic. Observer-bias will be very little because of the straightforward multiple-choice questions in forms D2 and D3.

The results will help to evaluate mesh repair for epigastric an umbilical hernia, and find a surgical device/method that minimizes the complication rate. Besides complication rate, recurrence and costs are taken in account.

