### Blinding

The trial is a patient-blinded type. The patient is informed on the type of mesh device used by means of the questionnaire after 24 months (P3). In the data handling phase of the, the annalist is blinded for treatment. The consulted physician during follow-up is not blind for the received treatment.

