### Definitions

A complication is defined as an undesired development that requires treatment, related to the operation site, occurring within 3 months postoperative. Treatment could also been initiated by the general practitioner, or other than that by the hospital surgeon. Complications are defined as following:

Extending operation time due to bleeding or other injury during the procedure

Prescribed medication treatment such as antibiotics and pain killers other than paracetamol after discharge

Re-operation such as evacuation of a haematoma, drainage of an abscess, exploration related to pain or intra-abdominal problems, or early recurrence

Wound care which requires more than once a day irrigation of the wound

Hospitalisation longer than scheduled or re-admission

The costs will be calculated post-hoc on the basis of the number of visits to the outpatient clinic, operation duration, costs of prosthesis and complication-related costs up to 2 years after the operation.

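### Multiple-choice forms do not keep observer bias small when the primary endpoint is made of treatment decisions and the follow-up doctor knows the device

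*Protocol article*

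**What the plan says.** All references are to the protocol article.

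- **Endpoint (Definitions).** "A complication is defined as an undesired development that requires treatment, related to the operation site, occurring within 3 months postoperative". The five listed components are a longer operation because of bleeding or injury; "Prescribed medication treatment such as antibiotics and pain killers other than paracetamol after discharge"; re-operation; wound irrigation above a set frequency; and "Hospitalisation longer than scheduled or re-admission". The treatment may be started by a general practitioner or someone else outside the surgical team.
- **Who knows the device (Blinding, Discussion).** Of the operator: "By all means, the operating surgeon cannot be blinded for the type of mesh". At follow-up: "The consulted physician during follow-up is not blind for the received treatment". The patient is blinded until the 24-month questionnaire, and in data handling "the annalist is blinded for treatment".
- **Why the outpatient doctor is not blinded (Discussion).** The authors accept that the doctor who completes D2 and D3 could be blinded, but write "Because of logistical reasons this is not added to this study protocol". They add that blinding would have little value, because "Observer-bias will be very little because of the straightforward multiple-choice questions in forms D2 and D3".
- **Where complications are collected (questionnaire sections).** On D2, by the doctor at one month, and on P2, by the patient at three months. D3, by the doctor at one year, lists recurrence, analgesics, pain and cosmetic scores, but not complications.
- **Timing (Publication).** The report on the primary endpoint is placed at one month. Objectives/Endpoints and Definitions both set a three-month window.

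**The concern.** The reason given answers a different question from the one that matters. The format of a form limits variation in how a known fact is recorded. Here the fact itself is that someone decided to treat: to prescribe, re-operate, prolong a stay or re-admit. If that person knows the device, the influence acts before any box is ticked.

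This is a superiority trial, and its main conclusion rests on this endpoint. The article itself says that the choice of mesh often reflects the surgeon's personal preference, so a difference in treatment threshold between devices is not far-fetched. A reader who accepts the sentence would set aside a real route for bias, for a reason that does not touch it.

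**Working it through.** **1. Each component against the blinding.**

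| Component | Who decides | Knows the device? |
|---|---|---|
| Operation extended by bleeding or injury | Operating surgeon | Yes |
| Medication prescribed after discharge | Hospital doctor or general practitioner | Hospital doctor yes; general practitioner not stated |
| Re-operation | Surgeon | Yes if the operator or follow-up doctor; otherwise not stated |
| Wound care above a set intensity | Hospital or outside care | Hospital doctor yes; outside care not stated |
| Longer stay or re-admission | Hospital | Largely yes |

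No component is free of a decision. The article gives no split of events by component or by decision-maker, so the share exposed to unblinded judgement is unknown.

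**2. The forms cited in the defence.** Of D2 and D3, only D2 lists complications. Half of the defence therefore concerns a form that does not feed the primary endpoint. The blinded source, P2, is not mentioned in the defence. If the primary report is really made at one month, P2 will not yet exist for it, and the report would rest on doctors' records alone.

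**3. How much a small differential could matter.** The plan gives no figure for bias, so this is an illustration.

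- Sample size, from the plan: 2 × 137 × 1.15 × 1.10 = 346.6, stated as 346. Allowing for the plan's 10% loss, 346 × 0.90 / 2 = 155.7, so n = 156 per arm.
- True rate: 20% in both arms (the plan's control rate). Assumption: recorded rates are 20% ± d/2.
- Standard error under the null: SE0 = √(2 × 0.20 × 0.80 / 156) = 0.0453. The critical difference is 1.96 × 0.0453 = 0.0888.
- SE1 = √([p1(1−p1) + p2(1−p2)] / 156).
- Rejection rate = Φ[(d − 0.0888)/SE1] + Φ[(−d − 0.0888)/SE1].

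| d | Recorded rates | SE1 | Two terms | Total |
|---|---|---|---|---|
| 0 | 20.0% / 20.0% | 0.0453 | 0.025 + 0.025 | 0.05 |
| 3 points | 21.5% / 18.5% | 0.0453 | 0.097 + 0.004 | 0.10 |
| 4 points | 22.0% / 18.0% | 0.0452 | 0.141 + 0.002 | 0.14 |
| 5 points | 22.5% / 17.5% | 0.0452 | 0.196 + 0.001 | 0.20 |

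The same shifts in the other direction would hide a true benefit of the patch.

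**4. What a restricted analysis can deliver.** Suppose re-operation and re-admission make up a share s of events, and the patch halves the risk as planned (20% against 10%). Expected events per arm are 31.2s and 15.6s. By the normal approximation for two proportions at 156 per arm, power is about 56%, 39% and 21% for s = 0.75, 0.50 and 0.25, against about 70% for the full endpoint. (The plan's sample-size calculation states 90%; that gap is a separate matter and nothing here depends on it.) The restricted analysis can describe, but it can seldom confirm.

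**The case against.** The case on the other side is substantial, and much of it stands.

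- *The endpoint is not wholly in the hands of unblinded surgeons.* A general practitioner may start treatment, the patient is blinded for two years, the analyst is blinded, and P2 already collects complications from the patient. This stands. A reader might infer that the endpoint is simply the unblinded surgeon's opinion; the document does not support that.
- *The lack of blinding is disclosed.* It is, with a practical reason. Only the further claim that the bias will be very small is at fault.
- *Supportive analyses do not escape the problem.* Re-operation is itself a surgeon's decision, so it is less discretionary rather than objective. On P2 the patient reports treatments that unblinded doctors partly ordered, so P2 addresses recording but not the decision. A patient under general anaesthesia cannot report the intra-operative component. All of this stands and limits what agreement between the analyses would prove.
- *A superiority claim should not depend on agreement.* This stands too. I simulated the planned 20% against 10% at 156 per arm. If re-operation and re-admission are 10% of events, that subset ties or points the wrong way in about 26% of the trials with a significant true benefit, and success falls from about 70% to 52%. The loss is about 9% of such trials at a 25% share and 1% at a 50% share. These shares are assumptions.
- *A sensitivity analysis may sit in a fuller plan.* Agreed. Its absence from an article is not the fault raised here.

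None of this rescues the stated reason: a multiple-choice format does not address how knowledge of the device affects the decision to treat.

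**Conclusion.** The point holds, in limited form. The sentence in the Discussion is unsound on the protocol's own definitions: the endpoint consists of treatment and management decisions, many are made or recorded by doctors who know the device, and the format of the form does not remove that influence. The one-month primary report also conflicts with the three-month window and, read literally, would leave out the only blinded report of complications.

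A reader might infer more: that the result will be biased towards the patch, or that the true false-positive rate is 10% to 20%. The document supports neither the size nor the direction of a differential. Those figures only show that shifts of 3 to 5 points, against a hoped-for effect of 10 points, would not be negligible. They rest on equal true rates of 20%, 156 analysed per arm and the normal approximation.

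**What to change.** 1. In the Discussion, delete or correct the observer-bias sentence, and state detection bias in the primary endpoint as a limitation.
2. Pre-specify two supportive, non-gating analyses of the primary endpoint:
   - (a) re-operation or re-admission only, described as less discretionary and not as objective;
   - (b) complications reported by the blinded patient on P2, with a stated recall period of 0 to 3 months and without the intra-operative component.
3. Report both beside the primary result and discuss any discordance. Do not make a superiority claim conditional on agreement.
4. Reconcile the one-month report under Publication with the three-month window under Objectives/Endpoints and Definitions, so that P2 is available when the primary endpoint is reported.

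The cost is a few sentences, a recall period on P2 and two short tables; the data are already planned and no extra assessor is needed. The downsides are few events and wide intervals in (a) and recall error in (b). Neither analysis removes bias in the treatment decisions themselves, and the report should say so.
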